### Blinding

Due to the distinct nature of the interventions, blinding of both participants and treating clinicians is not feasible. To maintain methodological rigor, a single-blind approach will be employed: all outcome assessments—including ultrasound measurements, VAS, and NDI scoring—will be conducted by an independent evaluator unaware of the group assignments. Statistical analyses will also be performed by a blinded third-party statistician to ensure impartial interpretation of data.

### Intervention

Cervical traction will be performed with participants in a supine position using a specialized traction apparatus. A cervical traction strap is then obtained for this procedure. The patient lies flat on the bed in a neutral supine posture, and protective cotton gauze is placed under the neck to prevent skin damage during traction. The cervical traction strap is secured beneath the patient's jaw and at the occipital protuberance. We make adjustments to ensure the appropriate tightness while directing traction towards the top of the head. The traction angle, which is the angle between the cervical spine and a horizontal plane during traction, usually ranges from 0° to 15°. The process is beginning with an initial weight will range from 1 to 3 kg, generally not exceeding one-tenth of the patient's body weight, and the specific traction angle and weight are adjusted based on the patient's will be modified according to comfort and the condition throughout the treatment. During traction sessions, the patient's head is stabilized, and family members or nurses are present to closely monitor the patient's condition. If the patient experiences dizziness or discomfort, the nursing staff notify the physician for immediate intervention. Each traction session lasts about 30 min, and is administered twice daily.

### Treatment group

Gentle muscle adjustment involves the physician sitting or squatting in front of the child's head after cervical traction. Using both hands, they employ various techniques such as pressing, kneading, pinching, and rubbing on the neck muscle groups to relieve muscle tightness and improve neck flexibility, with this process lasting about 10 min. Following this, passive micro-adjustment takes place, where the physician stabilizes both sides of the child's neck with their hands, placing their thumbs on the child's jaw and spreading their fingers across the occipital protuberance. With minimal force, the physician gently pulls upwards towards the top of the head to utilize the traction effect. The child is instructed to cooperate by performing passive neck flexion, extension, lateral bending, and rotation across six specific angles—namely, flexion, extension, left lateral bending, right lateral bending, left rotation, and right rotation, the angle of each movement direction should be approximately 5–10 degrees. During this process, the physician should apply gentle force to the joint capsule with minimal load, ensuring the entire procedure is performed slowly and softly to maintain comfort, lasting approximately five minutes.all done slowly and gently to ensure comfort, lasting around 5 min. Subsequently, during active micro-adjustment, the cervical traction is gradually released, allowing the child to sit on a treatment chair. The physician positions themselves behind the child, placing their thumbs near the GB20 (Gallbladder 20) point at the back of the neck and resting their remaining fingers on either side of the jaw. The physician acupoints and applies light opposing pressure to slightly elevate the cervical spine while guiding the child to actively perform flexion, extension, lateral bending, and rotation, emphasizing movement toward the restricted direction. This stage lasts approximately 10 min. Lastly, emphasizing the importance of muscle relaxation techniques for proper bone alignment, both hands employ gentle techniques, including pressing and kneading, on the child's neck and shoulder muscles. This approach is designed to relax the neck meridians and restore the muscles' physiological properties, and which in turn enhances neck flexibility and ensures the correct anatomical alignment of the atlanto-axial joint, ultimately achieving “bone alignment.” This final treatment phase lasts approximately five minutes and primarily involves gentle pressing and kneading to promote muscle relaxation. The entire treatment regimen is structured to be conducted twice daily, five days a week, over a span of two consecutive weeks. Figure 3 shows the demonstration of manual techniques.

**Figure 3 F3:**
[figure not shown]
Demonstration of manual techniques. **(A)** Kneading to relax the neck muscles; **(B,C)** micro-adjustment techniques to adjust muscle and skeletal balance; **(D)** Manipulative adjustment of atlantoaxial subluxation.

### Control group

After each cervical traction session, a properly sized cervical collar will be securely fastened around the child's neck, along with protective cotton gauze to reduce the risk of skin irritation. The child's head will be kept in a neutral forward position. Measures will be taken to stabilize it and prevent any lateral movements. The length of time the cervical collar is worn will depend on the child's comfort level, with the goal of keeping the collar on for as long as possible, although it will be removed during sleep. If the child experiences any discomfort while wearing the collar, the physician will be notified immediately. The cervical collar will be applied right after each traction session; the treatment plan consists of five sessions per week for two consecutive weeks.

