**Methods:**

This study utilized a randomized controlled trial design, where eligible patients diagnosed with AARS were, randomly assigned (1:1) to either a treatment group (gentle manipulative technique combined with continuous traction) or a control group (traction plus cervical collar immobilization). The treatment group received treatment twice daily, five days per week, for two weeks. The control group received the same traction protocol but wore a neck brace immediately after each traction treatment. The primary outcome measure was musculoskeletal ultrasound (MUSU) findings, while secondary outcomes include Visual Analogue Scale (VAS) pain scores and Neck Disability Index (NDI) scores. Both groups were assessed at baseline, post-treatment, two weeks, and six months after treatment.

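### The control arm's stated session count (10 in two weeks) does not match the twice-daily traction that both arms are said to share (20 in two weeks); the schedule statements need reconciling

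*Protocol article*

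**What the plan says.** Four places in the protocol article bear on how much traction each arm receives.

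- **Abstract, Methods.** For the treatment arm: "The treatment group received treatment twice daily, five days per week, for two weeks". For the control arm: "The control group received the same traction protocol but wore a neck brace immediately after each traction treatment".
- **Intervention.** This section comes before the two arm sections and is not limited to one arm: "Each traction session lasts about 30 min, and is administered twice daily".
- **Treatment group.** "The entire treatment regimen is structured to be conducted twice daily, five days a week, over a span of two consecutive weeks".
- **Control group.** "The cervical collar will be applied right after each traction session", and, in the same sentence, "the treatment plan consists of five sessions per week for two consecutive weeks".

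Two further places concern the timing of the manual work. The Treatment group section opens by placing that work after traction, but later says that "during active micro-adjustment, the cervical traction is gradually released, allowing the child to sit on a treatment chair". That step follows about 10 minutes of soft-tissue work and about 5 minutes of passive movement. The Discussion describes the technique as carried out with continuous traction maintained.

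**The concern.** Traction is the treatment that the two arms share; what is meant to differ is manipulation in one and a collar in the other. The Abstract and the Intervention section point to the same traction, twice daily, in both arms. The Control group section gives a weekly count that is half of what twice daily on five days produces. Because that sentence has just used the word session for a traction session, the natural reading is five traction sessions a week.

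Anyone delivering the control arm from that section as written would give half the traction that the Abstract implies. The Background credits relaxation under traction with lowering neck muscle tension and easing neck pain. Unequal traction would therefore bear on the primary stiffness outcome and on pain. It would be fully aligned with arm, so no analysis could separate it from the effect of manipulation.

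**Working it through.** **Inputs**

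- Session length: about 30 minutes (Intervention).
- Frequency: twice daily (Intervention; also Abstract and Treatment group).
- Days and weeks: five days a week for two weeks (Abstract and Treatment group). The Intervention section gives no days per week. For the control arm these are carried over from the Abstract's statement that the traction is the same.
- Control count: five sessions a week for two weeks (Control group).
- Manual work before traction is released: about 10 + 5 = 15 minutes (Treatment group).

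**Step 1. The control arm's own figure**

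5 sessions per week × 2 weeks = 10 sessions.

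**Step 2. The same quantity from the other statements**

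2 per day × 5 days × 2 weeks = 20 sessions, or 10 a week. The control figure of 5 a week does not reproduce.

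**Step 3. Scheduled traction minutes (sessions × minutes per session)**

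| Reading of the control sentence | Treatment arm | Control arm | Ratio |
|---|---|---|---|
| Five traction sessions a week (literal) | 20 × 30 = 600 | 10 × 30 = 300 | 2.0 |
| Five treatment days a week, twice daily | 20 × 30 = 600 | 20 × 30 = 600 | 1.0 |

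**Step 4. The secondary ambiguity, with session counts taken as equal**

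The article does not say whether the manual work done before release falls inside the 30-minute session, follows it, or extends it. As an assumption, let the extra traction be between 0 and 15 minutes per treatment-arm session.

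- Lower end: 20 × 30 = 600 against 20 × 30 = 600, ratio 1.0.
- Upper end: 20 × (30 + 15) = 900 against 600, ratio 1.5.

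The lower end holds both when the manual work comes after traction has ended and when it falls within the 30 minutes. No section states a 45-minute traction session; the upper end is a bound, not a figure from the article.

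**The case against.** The best defence is that the intended design is clear. The Abstract says that the traction is the same, and the Intervention section describes it once for everyone. In the disputed clause the grammatical subject is the treatment plan, not traction. It may simply be a loose way of saying five treatment days, in an article with other language slips. This is plausible, and it is why unequal traction cannot be treated as established. It does not remove the conflict: the sentence as printed gives a different number, and no other section corrects it.

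A second defence is that traction during manual work belongs to the tested package. The Objective and Trial design sections define the experimental arm as manual adjustment combined with continuous traction. This largely stands. A randomised comparison of the two packages is valid under every reading; what would be limited is attribution to manipulation as against collar. The wording about manual work after traction may also mean after traction has been set up, which would fit the later release and the Discussion. That part is an ambiguity, not a firm contradiction.

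A reader might go further and infer that the comparison is confounded, or that traction differs three-fold (900 against 300 minutes). The documents do not support either. The first ignores the five-treatment-days reading, under which the session counts are equal. The second stacks the literal session count on an added 15 minutes that the article never states.

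**Conclusion.** The point holds as an inconsistency in a rule that defines the comparator. The control arm's 10 sessions cannot be squared with the 20 implied by twice-daily traction that is the same in both arms. If the Control group section is followed literally, control-arm traction is halved (600 against 300 minutes, 2:1) and the Abstract's statement of identical traction is untrue. If five sessions means five treatment days, session counts are equal.

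The 2:1 figure assumes 30 minutes per session in both arms and full delivery of the schedule. The 1.0 to 1.5 range for the secondary ambiguity assumes equal session counts and 0 to 15 extra minutes per session. Confounding by traction is a possible consequence of the wording, not a demonstrated feature of the trial.

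**What to change.** Reconcile the Abstract, Intervention, Treatment group, Control group and Discussion into one statement of the number of traction sessions and the minutes of traction in each arm. State in the same place whether the manual work takes place within, after, or in addition to the traction session.

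If the amounts are meant to differ, remove the statement that the control arm has the same traction, and limit the conclusion to a comparison of the two treatment packages. Which schedule is right is for the clinical team.

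The cost is a short edit to the text. Sample size, outcomes and analysis are unaffected.

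### The control arm's session schedule contradicts the shared traction schedule: five sessions a week in one place, two a day in others

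*Protocol article*

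**What the plan says.** Four places in the protocol article bear on how often children receive traction.

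- Abstract, Methods: for the treatment arm, "The treatment group received treatment twice daily, five days per week, for two weeks". For the control arm, "The control group received the same traction protocol but wore a neck brace immediately after each traction treatment".
- Intervention, which comes before both arm sections and names neither arm: "Each traction session lasts about 30 min, and is administered twice daily".
- Treatment group: "The entire treatment regimen is structured to be conducted twice daily, five days a week, over a span of two consecutive weeks".
- Control group: "The cervical collar will be applied right after each traction session", and in the same sentence, "the treatment plan consists of five sessions per week for two consecutive weeks".

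The article gives no session total for either arm.

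**The concern.** Traction is the common background. The trial is set up so that the arms differ in what is added to it: the manual technique in one, the collar in the other. That contrast can be interpreted only if the background is the same in both arms. The Control group section states a weekly count that, taken at face value, is half the count given for the treatment arm.

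The article's own rationale makes traction dose relevant to the outcomes. The Background section says that the relaxation promoted under continuous traction lowers neck muscle tension and improves neck pain and head tilt. The primary outcomes are muscle thickness and Young's modulus, and pain is a secondary outcome. If control children had fewer traction sessions, a difference in stiffness, pain or efficacy rate could come partly from traction and yet be reported as an effect of the technique. If more traction helps, the bias would favour the treatment arm. Because dose would go with arm, no analysis could cleanly separate the two afterwards.

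**Working it through.** There is no stated total to reproduce, so the check is to derive the session count that each section implies and compare them.

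Formula: sessions = sessions per day × days per week × weeks, or sessions per week × weeks where only a weekly count is given.

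1. Treatment arm (Abstract and Treatment group): 2 × 5 × 2 = 20 sessions.
2. Control arm, Control group section read literally: 5 × 2 = 10 sessions.
3. Control arm, from the Abstract (same traction as the treatment arm) and the Intervention section (two a day): 2 × 5 × 2 = 20 sessions. The Intervention section gives no number of days per week, so the five-day week is taken from the Abstract and the Treatment group section.
4. Ratio of the two control-arm figures: 10 / 20 = 0.50.

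Minutes, assuming 30 minutes of traction per session in both arms: 20 × 30 = 600 and 10 × 30 = 300. This is rougher than the session count for two reasons. The Intervention section gives 30 minutes only as an approximate length. The Treatment group section also leaves the end of traction unclear: it places the manual work after traction, yet has traction released only at the active adjustment stage.

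Two readings might remove the conflict.

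- The weekly count of five refers to collar applications, not traction. This fails, because the same sentence ties a collar application to every traction session. Ten traction sessions a week would mean ten applications.
- The weekly count of five means five treatment days. Then 2 × 5 × 2 = 20 in both arms and all four places agree. This is possible, but it needs the word session to mean a day. The Intervention section uses it for a single traction period of about half an hour given twice a day, and the Control group sentence itself uses it for one traction period.

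**The case against.** The strongest reply is that this is loose wording and not a different schedule. Two of the four places already cover control-arm traction and point to equality: the shared Intervention section applies to everyone, and the Abstract says outright that the traction is the same. The Control group section is mainly about the collar and never says that traction is given once a day. Reading five sessions as five days reconciles everything. The envelope instructions that staff would follow are not shown, so nobody can say from the article what will be delivered.

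Much of this stands. A reader might infer that control children will receive half the traction, or that the investigators chose an unequal background. The documents support neither: the stated intent is equal traction, and a reconciling reading exists. Nor can a two-fold difference in attendances be inferred, because the article does not say whether two sessions on one day mean two visits.

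What does not stand is that the text is clear enough as it is. The reconciling reading gives a word a meaning that it does not have elsewhere in the article, and the two arm sections describe what should be one schedule in different terms. Nor is this detail that a journal article can leave to the full protocol: the article states a schedule for the control arm, and that statement conflicts with its others.

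**Conclusion.** The point holds as an internal contradiction in the control arm's session schedule. Read literally, the Control group section gives 10 sessions; the Abstract and Intervention sections, on a five-day week, imply 20. The factor of two in sessions depends only on that literal reading. The figures of about 600 and 300 minutes depend in addition on 30 minutes of traction per session in both arms, which the article does not firmly fix.

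The consequence is conditional. If the Control group wording is followed literally, the comparison of technique with collar is confounded with traction dose. If five sessions means five days, the session counts are equal and only the wording is at fault. The article alone does not settle which applies. The ambiguity should be removed, because a difference in delivered background treatment cannot be repaired once the children have been treated.

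**What to change.** Reconcile the Abstract, Intervention, Treatment group and Control group sections into one statement of sessions per day, days per week and weeks that expressly covers traction in both arms, and have both arm sections refer to it. Carry the same statement into the instructions in the randomisation envelopes. Which schedule is right is for the investigators to decide; this review proposes none.

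As an optional check, tabulate the traction sessions delivered by arm, so that the report can show whether the background treatment was in fact equal.

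The cost is a short textual amendment and a check of the envelope instructions against it. The clarification needs no additional patients. The optional table needs a session count for each child.

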### Outcome measures

#### Primary outcome

The primary measures of interest included muscle thickness that encompasses both the anterior-posterior dimension (APD) and the lateral dimension (LD), along with the Young's modulus value (E value).

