##### Measurement location

The anatomical site for measuring the sternocleidomastoid muscle will be taken at the midpoint between the sternal notch and the mastoid process. In the case of the trapezius muscle, the measurement location will begin 2 cm lateral to the C4 spinous process for the trapezius (35).

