### Statistical analysis

All data will be analyzed using SPSS version 22.0 software. Categorical data will be summarized as frequencies or percentages and compared using Chi-square tests. Ordinal data will be analyzed using rank-sum tests. For measurement data that follow a normal distribution and demonstrate homogeneity of variance, results will be presented as mean ± standard deviation (x ± s). Independent samples t-tests will be used for between-group comparisons, paired-sample t-tests for within-group comparisons. Non-normally distributed data will be analyzed with nonparametric rank-sum tests. A *P*-value < 0.05 will be considered statistically significant.

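### Three co-equal primary ultrasound measures on two muscles, each tested at P < 0.05 with no rule for success, leave at least six chances of a positive primary result

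*Protocol article*

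**What the plan says.** Under Outcome measures, the Primary outcome section lists several measures with equal standing: "The primary measures of interest included muscle thickness that encompasses both the anterior-posterior dimension (APD) and the lateral dimension (LD"). The same sentence gives a third measure, elasticity, the same status. The abstract is broader still: "The primary outcome measure was musculoskeletal ultrasound (MUSU) findings".

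The Positioning and Measurement location sections apply the examination to two muscles. For the first: "The anatomical site for measuring the sternocleidomastoid muscle will be taken at the midpoint between the sternal notch and the mastoid process". For the second: "In the case of the trapezius muscle, the measurement location will begin 2 cm lateral to the C4 spinous process". Neither section mentions left, right or symptomatic side.

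On timing, the abstract says: "Both groups were assessed at baseline, post-treatment, two weeks, and six months after treatment". It does not say which outcomes are taken at which visit.

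The Statistical analysis section prescribes separate independent-samples t-tests between groups, or rank-sum tests where data are not normal. It has one decision rule, that a P-"value < 0.05 will be considered statistically significant". It ranks no measures and does not say how many primary measures must be positive.

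**The concern.** A 5% significance level describes the error rate of a trial's main conclusion only when one test, or one stated rule for combining tests, decides that conclusion. Here three measures on two muscles share primary status and nothing says how they combine. After the data are seen, a single significant result among six could be presented as success on the primary outcome, and the protocol would not contradict it.

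This matters because the Discussion and Conclusion rest the trial's value on objective quantification of efficacy by ultrasound. The sample size does not reveal an intended lead measure either. It is built on an efficacy rate, which the protocol lists among the secondary outcomes.

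A related gap is the direction of benefit. The Background reports that neck muscles are stiffer in these children, so a lower E value can be read as benefit. Nothing says whether a larger or smaller APD or LD is favourable. That makes a thickness result hard to interpret. It adds no multiplicity, because a two-sided 5% test already covers both directions.

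**Working it through.** **The plan's own figure.** The protocol gives no family-wise error rate to reproduce. Its one design calculation, in Statistical methods, uses p1 = 0.935 and p2 = 0.736:
- p = (0.935 + 0.736)/2 = 0.8355; q = 0.1645.
- n = 8pq/(p1 − p2)² = 8 × 0.8355 × 0.1645 / 0.199² = 27.76, rounded up to the stated 28.

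The figure reproduces. It concerns an efficacy rate, so it does not identify a lead ultrasound measure.

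**Inputs for the error rate**
- Measures: APD, LD and E value = 3 (Primary outcome).
- Muscles: sternocleidomastoid and trapezius = 2 (Positioning; Measurement location).
- Tests at one visit: 3 × 2 = 6.
- Level per test: 0.05 (Statistical analysis). Two-sided is assumed, since sidedness is not stated.
- Success rule: not stated. The calculation assumes that any one significant result counts.
- Correlation between tests: not given. The range 0 to 0.9 is an assumption.

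**Independent tests.** Chance of at least one false positive = 1 − 0.95^k:
- k = 3 (one muscle only): 1 − 0.95³ = 14.3%.
- k = 6 (both muscles, one visit): 1 − 0.95⁶ = 26.5%.
- k = 18 (six tests at three visits): 1 − 0.95¹⁸ = 60.3%.

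**Correlated tests.** Test statistics were simulated under the null as Z_j = √ρ·f + √(1 − ρ)·e_j, with f and e_j standard normal, and a false positive counted if any |Z_j| > 1.96 (300,000 draws):

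| Assumed ρ | 3 tests | 6 tests | 18 tests |
|---|---|---|---|
| 0 | 14.3% | 26.5% | 60.3% |
| 0.3 | 13.6% | 24.1% | 50.8% |
| 0.5 | 12.5% | 20.6% | 39.8% |
| 0.7 | 10.9% | 16.5% | 27.8% |
| 0.9 | 8.4% | 10.8% | 15.1% |

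**Does the 18-test column apply?** The passages point in different directions:
- The abstract lists three post-baseline assessments for both groups, which allows ultrasound at each.
- Follow-up observation ties the two-week and six-month visits to whether symptoms return or improvement lasts, and does not mention ultrasound.
- The last paragraph of the Background and the Conclusion describe muscle change from pre- to post-treatment.
- The schedule is in Figure 2, which is not available here.

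The 18-test figures are therefore conditional. The six-test figures need only the post-treatment visit.

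**The case against.** The strongest objection is that the statistical analysis plan is not shown and that this article condenses a fuller protocol. Adjustment methods and testing order are often left to those documents, so the absence of a multiplicity procedure would not be a finding by itself. That is right, and the point does not rest on it. It rests on what the article itself fixes: a dedicated primary-outcome section naming three co-equal measures, detailed instructions for two muscles, and one threshold for every test.

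A second objection is that success might require all measures to be significant. The false-positive rate would then not exceed 5%, and the difficulty would be power. The document does not say so. The inflation is therefore one open reading and not a settled property of the trial.

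A third is that the measures may be strongly correlated. At an assumed 0.9 the six-test figure falls to about 11%. That is still about twice the nominal level, but well short of the independence figure.

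A reader might also infer a larger problem: ultrasound tested at all three post-baseline visits, or on both sides of the neck as well, giving 36 tests and 1 − 0.95³⁶ = 84% under independence. The documents do not establish this. Ultrasound at every visit is only an inference from the abstract. No passage says that both sides are measured; the text gives one site per muscle. That the condition is asymmetric makes the silence on side a gap in the definition, but it does not double the number of tests.

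**Conclusion.** The concern holds at the level of six tests. The protocol fixes three co-equal primary measures on two muscles at P < 0.05 each, and leaves the lead measure, muscle, side, visit and success rule undetermined. If any one significant result counts as success, the false-positive chance at the post-treatment visit alone is 26.5% under independence and about 24% to 11% at assumed correlations of 0.3 to 0.9. If ultrasound is also analysed at two weeks and six months, it is up to 60% under independence and about 51% to 15% over the same correlations. That extension is conditional on a schedule the text leaves unclear. Analysing both sides would raise the figures further, but nothing shows that this is planned.

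The conclusion depends on the any-one-counts reading, which the document permits but does not state, and on correlations that it does not give.

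**What to change.** Before unblinding, name one primary variable by measure, muscle, side and visit, with side defined before randomisation and the direction of benefit stated. One example is the E value of the sternocleidomastoid on the symptomatic side at the post-treatment visit, lower being better. The sponsor may prefer another. Make all other ultrasound measures and visits secondary. This restores a 5% error rate for the primary conclusion.

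If several measures stay primary, fix the muscle, side and visit for each and apply Holm at a family-wise 5% across every retained primary test. For six tests the first step is 0.05/6 = 0.0083. Applying Holm to APD, LD and E value alone, with muscle, side and visit still open, would not be enough.

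The change is to protocol and registry wording and needs no added procedures. It has two costs:
- **Status or stringency.** The other ultrasound measures lose primary status or face a stricter threshold. With 35 per group, the standardised difference detectable with 80% power is (1.96 + 0.84) × √(2/35) = 0.67 at 0.05, and 0.83 at 0.0083. With about 30 per group after 15% dropout (35 × 0.85 = 29.75), these become 0.72 and 0.90.
- **Sample size.** The protocol should state that its sample size came from an efficacy rate and was not derived for the chosen ultrasound variable.
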